### Quality assurance

We will educate all practitioners and set qualification standards to make sure the patients are treated with high standards and in accordance with the trial protocol.

Treatment will be administered by doctors of Korean Medicine who have extensive clinical experience with heating and cooling stimulation therapy and moxibustion and the following qualifications: (i) graduate of a 6-year full-time course in Korean Medicine, taught as a college program; (ii) certified by the Korean Ministry of Health and Welfare as a Korean Medicine Doctor; (iii) more than 1 year of postgraduate clinical training in an Oriental medicine hospital; and (iv) completion of the first-year residency program in our Department of Acupuncture and Moxibustion.

Practitioners and medical equipment managers will attend a 2-day training workshop about the treatment programs and will be educated on selection of acupoints by using a pressure algometer. Medical equipment managers will also be educated on measuring skin temperature and setting the treatment and sham devices. A written protocol and standardized recording documents will be provided. Because the relationship between a practitioner and patient could influence the results, all such interactions will be strictly limited, except when reporting side effects. All practitioners and outcome assessors will be blinded to group allocations, and medical equipment managers will not participate in the interventions. To assure blinding of patients, we will put a small fabric curtain next to the device to block the patient’s view.

### Analysis of data

A VAS will be used to assess the effect of treatment. The primary endpoint is the change in the 100 mm Pain VAS from baseline (before treatment) to 4 weeks [10, 12, 17]. The 100 mm VAS is widely used because it provides reliable and valid measurements of pain intensity [18]. Each patient will be asked to check their pain intensity along an ungraded 100 mm horizontal line, where ‘0’ represents ‘no pain’ and ‘100’ represents ‘unbearable pain’.

The secondary endpoints are change from baseline in three evaluations of functional disability (Korean Oswestry disability index [KODI], Korean Roland Morris Disability Questionnaire [KRMDQ], and Traditional Medicine Back pain Questionnaire [TMBQ]) and three evaluations of range of motion (ROM) (modified Schöber test, finger-to-floor distance, and finger-to-thigh distance). These parameters will be measured at baseline, 2 weeks, 4 weeks, and at 4 weeks after the last treatment.

The KODI has 10 criteria related to daily living activities and each item has six possible responses, ranging from ‘no problem’ to ‘not possible’. The KODI focuses on a limitation in the range of physical functions, including standing, walking, lifting, sitting, lying down, dressing, and personal care [18]. We excluded questions about sexual activities because many subjects do not provide honest answers about their sex lives, and it is hard to account for subjects who are single. The KRMDQ contains 24 yes/no queries and also focuses on limitations in physical functions, including walking, bending over, sitting, lying down, dressing, sleeping, self-care, and daily activities. The KRMDQ is easy to understand, interpret and score. Higher scores in the KRMDQ and KODI indicate greater disability [18]. We will use Korean versions of these surveys, which have documented reliability and validity [19, 20]. The TMBQ evaluates low back pain and is based on traditional Korean medicine [21].

The modified Schöber test measures the curvature of the spine. In this test, the lumbosacral junction is marked on the back; a second mark is placed 5 cm below the junction, and a third mark is placed 10 cm above the junction. Then the subject is asked to bend forward as far as possible, and the new distance between the second and third marks is measured [22]. We will also use a digital flexibility testing device (Standing Trunk Flexion meter TKK5403, Takei Co., Japan) to assess the trunk flexibility, finger-to-floor distance (distance between the fingertips and the floor after forward flexion with knees straight, while on a 20-cm high box) [23], and finger-to-thigh distance (distance between the fingertips and the floor after lateral bending with knees straight, while on a 20-cm high box) [24].

### Safety assessments

Any physical or clinical changes will be reported by the assessor, practitioner, and patient at each visit. All symptoms, date of onset, and duration will be recorded.

### Sample size

The primary endpoint will be change in 100 mm VAS score after 4 weeks of treatment. Liu *et al*. [25] previously showed that the 4-week change was 7.6 for the test device and 3.9 for the control device. Patients will be randomized to the test and sham groups in a 1:1 ratio. Assuming a reference standard deviation (SD) of 5.37, power analysis indicates that a sample size of 34 has an 80 % probability of yielding a significant difference at the level of 0.05. In order to achieve stronger results, a one-sided 97.5 % lower confidence limit for the treatment difference (VAS on test device - VAS on sham device) will be greater than 0. We will allow for a 15 % dropout rate by randomization of 40 subjects to each group.

### Statistical analysis

All data will be analyzed using SAS version 9.1 (SAS institute Inc. Cary, NC, USA). All statistical tests will be two-sided, and the level of significance will be set at 0.05. Continuous variables will be expressed as means ± SDs and categorical variables as numbers and percentages. For analysis of the primary endpoint, the two-sided 95 % confidence interval will calculated by analysis of covariance (ANCOVA) and the model will include fixed-effect for study site. Student’s *t*-test will be used for evaluation of primary and secondary end-points. Categorical data will be analyzed using Pearson’s chi-square test or Fisher’s exact test, as appropriate.

For safety analysis, the numbers and percentages of patients will be presented in a frequency table. Patients with adverse events will be listed along with their medical histories and concomitant medications, with start and stop dates. Categorical variables will be summarized by frequency tables, and continuous laboratory variables, and changes from baseline will be expressed by summary statistics. In addition, the number and percentage of patients with each value below, within and above the normal range will be tabulated, and “shift tables” (summaries of individual changes in laboratory parameters) will be generated.

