### Randomization and blinding

Randomization will be performed by an independent statistician using a computerized random-number generator through the block-randomization method of SAS version 9.1 (SAS Institute Inc. Cary, NC, USA). Separate randomization files will be created for each study site. Allocation concealment will be maintained by use of opaque sealed envelopes. After the researcher screens a patient for inclusion and receives signed informed consent, the next envelope in the sequence will be accessed and opened by the certified Korean Medicine Doctor who supervises the medical device, immediately prior to treatment. A total of 80 participants will be randomly and blindly assigned to a treatment group or a sham group. All subjects, practitioners, and the outcome assessor will be blinded to group assignment. Blinding of the certified Korean Medicine Doctor who supervises the medical device and sets up the treatment (medical equipment manager) is not possible. The patients will be told: “You will be treated with one of two heating and cooling combination treatments. One has a large range of temperature change and the other has a small range of temperature change.”

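### The primary endpoint is given both an ANCOVA interval naming only study site and an unadjusted t-test, unranked; one model with baseline VAS and site would settle it at no cost

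*Protocol article*

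**What the plan says.** All places are in the protocol article, Methods/Design.

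- **Endpoint** (Analysis of data): "The primary endpoint is the change in the 100 mm Pain VAS from baseline (before treatment) to 4 weeks".
- **First method** (Statistical analysis): the two-sided 95 % interval for the primary endpoint comes from "analysis of covariance (ANCOVA) and the model will include fixed-effect for study site". Site is the only term named.
- **Second method** (Statistical analysis, next sentence): a Student's t-test "will be used for evaluation of primary and secondary end-points". It therefore covers the primary endpoint and the six secondary ones.
- **Level** (Statistical analysis): "All statistical tests will be two-sided, and the level of significance will be set at 0.05".
- **Success criterion** (Sample size): a one-sided 97.5 % "lower confidence limit for the treatment difference (VAS on test device - VAS on sham device) will be greater than 0". The model that produces the limit is not named there.
- **Design** (Randomization and blinding): "Separate randomization files will be created for each study site". Allocation is thus separated by site.

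**The concern.** One endpoint has two inferential methods and no order between them. If they differ, the interval and the p-value can point in different directions, and whoever reports the trial has some freedom over which to rely on.

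The t-test also leaves out the site by which allocation is separated, and it uses the pre-treatment VAS only by subtraction. The ANCOVA sentence does not name baseline VAS either, although every participant has one (Table 1). At stake are a single, pre-stated confirmatory test and the precision that baseline adjustment may bring.

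**Working it through.** **Inputs from Sample size.** The 4-week changes are 7.6 and 3.9, so the difference is 3.7. The SD is 5.37, taken here as the SD of change. Power is 80 %, n is 34 per arm and dropout 15 %. The level is two-sided 0.05.

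**Inputs assumed, because the article gives none.** The baseline/week-4 correlation r is 0.3, 0.5 or 0.7. The site effect is 0.3 SD of change, with two equal sites. SDs are equal at the two times unless stated.

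**Step 1: the plan's own figure.** n = 2 × [5.37 × (1.960 + 0.842) / 3.7]² = 33.07, so 34 per arm, and 34 / 0.85 = 40. Both figures reproduce. Power at 34 is 81.1 % by the normal formula and 79.9 % by the noncentral t. The calculation is that of an unadjusted two-sample comparison of change.

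**Step 2: ANCOVA with site only.** Simulation at 34 per arm used 20,000 null replicates and 8,000 at the planned effect for each r.

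| | r = 0.3 | r = 0.5 | r = 0.7 |
|---|---|---|---|
| Null: either test rejects | 5.0 % | 4.9 % | 5.0 % |
| Planned effect: t-test power | 79.7 % | 79.4 % | 79.4 % |
| Planned effect: site-only power | 80.4 % | 80.1 % | 80.0 % |
| Planned effect: either rejects | 80.5 % | 80.2 % | 80.1 % |

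Discordance is 2 × P(either) − P(first) − P(second). At the planned effect it is 0.8–0.9 %, so the two methods are practically one.

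**Step 3: ANCOVA with baseline and site.** With equal SDs, the ratio of ANCOVA variance to change-score variance is (1 − r²) / [2(1 − r)] = (1 + r)/2.

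| | r = 0.3 | r = 0.5 | r = 0.7 |
|---|---|---|---|
| Variance ratio | 0.65 | 0.75 | 0.85 |
| Power at 34, normal formula | 94 % | 91 % | 87 % |
| Power at 34, simulated | 93.0 % | 89.3 % | 85.2 % |
| Planned effect: either this or the t-test rejects | 94.1 % | 90.8 % | 87.0 % |
| Planned effect: discordance with the t-test | 15.5 % | 12.9 % | 9.4 % |
| Null: either rejects | 7.2 % | 7.1 % | 6.8 % |

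Example of discordance at r = 0.3: 2 × 94.14 − 79.74 − 93.01 = 15.5 %. A separate set of runs gave 16, 13 and 10 % discordance and 7.4, 7.1 and 6.4 % null rejection.

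**Step 4: unequal SDs.** Let k be the week-4 SD divided by the baseline SD. The ratio becomes k²(1 − r²) / (1 + k² − 2rk). At an assumed k of 1.4:

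- r = 0.3: 1.784 / 2.12 = 0.84, power about 86 %.
- r = 0.5: 1.47 / 1.56 = 0.94, power about 82 %.
- r = 0.7: 0.9996 / 1.00 = 1.00, power about 79 %, so no gain.

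A larger week-4 SD is plausible, because entry requires a VAS over 40 mm (Participants), which narrows the baseline spread.

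**The case against.** The strongest reply is that the article already points to the deciding analysis. The Sample size section sets success on a one-sided 97.5 % limit, which is the lower end of a two-sided 95 % interval, and Statistical analysis assigns the primary 95 % interval to the ANCOVA. This stands in part: a reader might infer that nothing indicates which result decides, and that is too strong. But the link is implicit, and the t-test is still assigned to the primary endpoint without being called supportive.

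Second, the ANCOVA sentence does not say that site is the only term. The name implies a continuous covariate, and baseline VAS is the natural one; a full covariate list may sit in a document not shown. This also stands, so the absence of baseline from the sentence is not by itself an error. The unranked t-test remains under either reading.

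Third, a t-test on change is valid in a randomised trial and matches the sample size calculation. That is correct. Preferring ANCOVA, also for the secondary endpoints, is a matter of efficiency.

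Other stronger readings are not supported:

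- **Lost precision in the planned ANCOVA together with inflated error.** The two exclude each other. The first needs an ANCOVA without baseline, the second one with it.
- **The t-test ignores baseline.** On change scores it subtracts baseline; it omits it only as a covariate.
- **Change scores over-correct whenever the correlation is below 1.** The relevant quantity is the slope r × k. At r = 0.7 and k = 1.4 it is 0.98, close to the slope of 1 that subtraction uses.

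**Conclusion.** The point holds as a free improvement. Two methods are stated for the primary endpoint, unranked, and the success limit is not expressly tied to either.

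The size depends on the reading. With site only, the choice between methods hardly matters (type I error about 5 %, discordance under 1 %). What is forgone is power of about 85–93 % against about 80 % at 34 per arm. With baseline in the ANCOVA, the methods disagree in about 10–16 % of trials at the planned effect, and accepting either as success gives about 6.5–7.5 % type I error instead of 5 %.

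These figures rest on assumed correlations of 0.3–0.7, equal SDs, a site effect of 0.3 SD and 5.37 being the SD of change. With a larger week-4 SD the power gain shrinks and can be nil.

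A reader might infer that the trial is mis-sized or that the defect must be fixed before the trial can be interpreted. Neither follows. The 34 and 40 per arm reproduce and stay sufficient, both methods are valid singly, and the stated success criterion already leans towards the ANCOVA interval.

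**What to change.** State one primary model: ANCOVA of the change in VAS (or of the week-4 VAS) on treatment, baseline VAS and study site. With baseline in the model both outcomes give the same treatment estimate, apart from the sign convention. Take the two-sided 95 % interval, the p-value and the confidence limit in the Sample size section from this model.

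Label the t-test of the primary endpoint an unadjusted sensitivity analysis, or remove it. Use the same form for the six secondary endpoints, each with its own baseline value plus site.

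The cost is wording only. Site and baseline are already part of the planned data, and no change to the sample size is needed. Trial status says recruitment was still ongoing, so the change could be made before unblinding.

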## Discussion

This clinical research aims to evaluate the safety and efficacy of OCH-S100, a device designed to administer heating and cooling combination therapy and provide relief for patients with chronic low back pain.

Heating and cooling therapy is widely used for treatment of musculoskeletal pain in clinical practice [7, 11]. The beneficial effects of this therapy may be mediated by changing blood flow, decreasing inflammation, induction of contraction and relaxation of blood vessels, decreasing edema, or decreasing stiffness of the muscle [11], but the underlying mechanism has not yet been proven. Moreover, there is only limited research on the efficacy of heating and cooling combination therapy. Thus, the clinical research described here is one of the few studies to test rigorously the efficacy and safety of heating and cooling combination therapy. Our research was designed to be rigorous, in that it will employ two study centers, double blinding of all assessors and practitioners, prior education of all practitioners, and fabric curtains to block patients’ view of the device. Moreover, a certified Korean Medicine Doctor with extensive experience will be treating all patients.

The device used in this research can precisely deliver temperatures from 15 °C to 45 °C, temperatures that do not burn or damage the skin. Therefore, this research will be able to document the effect of stimulation of the cold, cool, warm, and hot receptors on patients with chronic low back pain.

## Trial status

Patient recruitment is ongoing. Enrollment and trial completion is expected by the end of 2015.

## Abbreviations

ANCOVA: analysis of covariance
IRB: Institutional Review Board
KODI: Korean Oswestry Disability Index
KRMDQ: Korean Roland Morris Disability Questionnaire
ROM: range of motion
SD: standard deviation
TMBQ: Traditional Medicine Back pain Questionnaire
VAS: visual analog scale
